### Protocol non-adherence and missing data {20c}

Data analysis will be conducted according to the intention-to-treat method. Imputation of missing data is not planned. Additionally, a per-protocol analysis is planned as a sensitivity analysis to exclude participants who did not comply with the allocated intervention by missing the decision coaching or by failing to return all questionnaires.

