##### Decision coaching

Women in the IG will receive one or two (if required) 1-hour decision coaching sessions with a trained nurse supported by the DA. The nurse will, upon randomization in the IG, call these women to arrange an appointment for the decision coaching 2 weeks after being included in the study. The decision aid will be sent to the women by mail before the appointment.

The decision coaching is based on the Ottawa Decision Support Framework [37] and the nurse supports the decision-making process following these steps:
Clarification of the decision situation: What are the options? Where does the woman stand in her decision making process?Identifying support needs: What does the woman know about her personal risks due to the *BRCA1/2* mutation and the prevention strategies?Providing information and advice on the individual risks and prevention strategies according to the information of the evidence-based decision aid.Support in clarifying individual values and preferences.Support in weighing the different options.Clarification of the practicability of the alternatives for action in the woman’s life context.Communication of the decision.

The decision coaching is structured by patient decision guidance adapted to the special decisional needs of women with *BRCA1/2* mutation. Women and nurses can document the decision-making process within the decision guidance. In addition, the nurse will be prepared with fact sheets that provide essential information about the prevention strategies.

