### Explanation for choice of comparators {6b}

The comparator group in this trial (control group) will receive optimized standard care only (see the “Intervention group” section). Women will not be given any additional patient information and will not be invited for a coaching session. Standard care comprises at least one physician encounter in which women are informed about their diagnoses and the prevention options. In this study, women in the intervention as well as the CG will have at least one more physician consultation in which any open questions can be clarified and the woman is able to communicate her decision. This consultation can take place on site in the clinic or by phone.

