## Statistical methods

### Statistical methods {20a}

Baseline data will be analyzed to guarantee comparability of both groups. Mean differences of the primary outcome in both groups (congruence between preferred role at baseline and actual role in the decision-making process at t1) will be compared using an independent samples one-sided *t*-test with the group allocation as the independent variable. All secondary outcomes will be analyzed via independent samples *t*-tests, Chi-square tests, or nonparametric tests in case of non-normality. Beyond group allocation, demographic data will be used as the independent variable. All data analysis will be performed with SPSS and R.

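### The per-protocol exclusions can act on one arm only, and for the primary outcome they also discard women whose data are complete; both can introduce selection bias of unknown size and direction

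*Protocol article*

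**What the plan says.** Section {20c} of the protocol article, on non-adherence and missing data, makes three statements. The main approach is intention-to-treat: "Data analysis will be conducted according to the intention-to-treat method". Missing values stay missing: "Imputation of missing data is not planned". Then "Additionally, a per-protocol analysis is planned as a sensitivity analysis", which is to "exclude participants who did not comply with the allocated intervention by missing the decision coaching or by failing to return all questionnaires".

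The section Decision coaching places the coaching in the intervention group: "Women in the IG will receive one or two (if required) 1-hour decision coaching sessions". Section {6b}, on comparators, says of control women that they "will not be invited for a coaching session".

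Section {20a} defines the primary outcome as "congruence between preferred role at baseline and actual role in the decision-making process at t1". Table 1 in section {12} has no Control Preferences Scale item at 6 months. The time-point labels vary (12 weeks is t1 in {12} and {20a}, but T2 in the subsection describing the scale), but the primary time point is 12 weeks throughout. The section Baseline data and allocation says that a woman is randomised only after her baseline questionnaire has come back.

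**The concern.** A sensitivity analysis should show whether the main result survives a change in a doubtful assumption. This one changes the population by exclusions made after randomisation.

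- **Coaching criterion.** It compares intervention women who attended with all control women, including those who would not have attended had they been invited. Randomisation does not protect that contrast. No matching criterion is set for controls, although both groups are due a second physician encounter.
- **Questionnaire criterion.** It treats the return of forms as compliance with the intervention, which it is not. For the primary outcome it makes inclusion depend on a form that comes later and carries no part of that outcome.

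At stake is the interpretation. If the per-protocol result is set beside the intention-to-treat result as support for it, a difference produced by selection could pass as corroboration, or could mask a real effect.

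**Working it through.** **Which women each criterion removes (primary outcome)**

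1. Missed coaching: possible only in the intervention group, because controls are not invited.
2. Baseline form missing: no randomised woman, because baseline return precedes randomisation.
3. 12-week form missing: already out of the main analysis, because nothing is imputed.
4. 12-week form present, 6-month form missing: complete primary outcome, yet excluded. This is the only additional effect of the questionnaire criterion on the primary outcome.

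**The plan's own figure**

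The article gives no figure for the per-protocol set. The only design figure is 398 women (199 per group), for d = 0.3, power 0.8, alpha 0.05 and 30% drop-out. A one-sided t-test needs 139 per group, and 139 / 0.7 = 198.6, hence 199 per group and 398 in total. A two-sided test needs 176 per group, and 176 / 0.7 gives 252 per group and 504 in total. The sidedness is a separate matter; 139 per group is used below only as a working number of evaluable women.

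**Possible bias from the coaching criterion (illustration)**

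Assumptions, none of them in the document: the outcome is standard normal, there is no treatment effect, and a fraction q of intervention women do not attend. Attendance depends on a latent variable with correlation ρ to the outcome. With c = Φ⁻¹(q), the spurious difference is

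bias = ρ · φ(c) / (1 − q)

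For q = 20%: c = −0.842, φ(c) = 0.280, 0.280 / 0.8 = 0.350, and with ρ = 0.3 the bias is 0.105 SD.

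| q | ρ = 0 | ρ = 0.1 | ρ = 0.3 | ρ = 0.5 |
|---|---|---|---|---|
| 10% | 0 | 0.02 | 0.06 | 0.10 |
| 20% | 0 | 0.035 | 0.105 | 0.175 |
| 30% | 0 | 0.05 | 0.15 | 0.25 |

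A negative ρ gives the same values with the opposite sign.

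**Simulation with no true effect (139 per group, 4,000 trials, one-sided 0.05)**

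| Scenario | Mean difference (SD) | Rejection rate |
|---|---|---|
| No exclusions | 0.00 | 0.050 |
| q = 20%, ρ = 0.3 | 0.106 | 0.206 |
| q = 20%, ρ = 0; 10% lack 6-month form in each group, unrelated to outcome | 0.00 | 0.049 |
| No coaching exclusion; 10% lack 6-month form in each group, correlation 0.3 | 0.00 | 0.050 |
| No coaching exclusion; 6-month form missing in 5% (intervention) and 15% (control), correlation 0.3 | −0.045 | 0.023 |
| q = 20%, ρ = 0.3, with that 5% / 15% loss | 0.050 | 0.097 |

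The two criteria can therefore act in opposite directions.

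**Precision (SD units)**

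- All evaluable women: SE = √(1/139 + 1/139) = 0.120, one-sided power 0.80 at d = 0.3.
- 20% of intervention women removed: 111 against 139, SE = √(1/111 + 1/139) = 0.127, power about 0.76.
- A further 10% removed in each group for lacking the 6-month form: 100 against 125, SE = √(1/100 + 1/125) = 0.134, power about 0.72.

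**Complier-average causal effect**

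With attendance proportion p and no access in the control group, the estimate is the intention-to-treat difference divided by p. Without any effect, its target is zero whatever the link between attendance and outcome. At p = 0.8 its standard error is roughly 0.120 / 0.8 = 0.150. If the mailed decision aid alone shifts non-attenders by δ, the estimate is off by δ(1 − p)/p, which is 0.25δ at p = 0.8.

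**The case against.** One-arm exclusion is built into any per-protocol analysis of an add-on against usual care, and intention-to-treat remains the main analysis. That is true and limits the severity, but it does not make the contrast a randomised one.

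A reader might infer that the analysis will favour the intervention, on the view that non-attenders are less engaged and do worse. The document does not support this. The outcome is congruence of roles, and a woman who wants a passive role and gets one is fully congruent. Section {13} also admits carriers already in the screening programme, some of whom may skip coaching because their choice is settled. That could reverse the sign. Section {11c} plans calls, letters and rescheduling that may keep non-attendance low.

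A reader might also put a number on the valid outcomes lost by taking a share of 2 × 139 = 278. That may count drop-out twice, because the sample size section does not say whether its 30% applies at 12 weeks or through 6 months.

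Calling this the only sensitivity analysis in the trial would go too far. It is the only one that the article labels so, but the Discussion also plans a contamination analysis by family code, and a fuller plan may exist.

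Most secondary outcomes are measured at 6 months, where return of that form does matter, and a single per-protocol set across outcomes is common. That stands, so the deletion is needed for the primary outcome. The clause could be read as returning no questionnaire at all, but its ordinary sense is not returning every one.

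Finally, a complier-average estimate uses the same 12-week responders, so it does not repair missing outcomes. That stands too and must be stated with it.

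**Conclusion.** The point holds as a defect in how a secondary analysis is fixed. From the text alone, the coaching criterion can remove only intervention women, and the questionnaire criterion additionally removes women with a complete primary outcome while calling this non-compliance with the intervention.

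The consequence is a risk of selection bias, not a demonstrated bias. Its size and sign are unknown, because the document gives no attendance or return rates and no link between either and the outcome. It is zero if attendance and 6-month return are unrelated to the outcome. The illustrative range of 0 to 0.25 SD in either direction rests wholly on the assumed q of 10 to 30% and |ρ| of 0 to 0.5. The loss of precision from the questionnaire criterion is certain in direction and avoidable; its amount depends on how many 12-week responders lack the 6-month form.

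Nothing here undermines the intention-to-treat comparison itself.

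**What to change.** 1. For the primary outcome, delete the questionnaire clause from section {20c}, so that no woman with baseline and 12-week data is excluded for lacking the 6-month form. Define non-compliance by coaching attendance alone, and state what counts as having missed it.
2. Label the coaching-attendance analysis supplementary, and say that it is not confirmation of the intention-to-treat result.
3. Accompany or replace it with a complier-average causal effect estimate, using randomised allocation as the instrument and adjusting for baseline covariates. State three limits: the interval is wider; the decision aid mailed before the appointment can affect women who then do not attend, which weakens the exclusion restriction; and missing 12-week data are not addressed.

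The cost is a change of wording and one extra model, with no change to conduct or data collection. It should be made before outcome data are seen by group.

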### Public access {31c}

The datasets analyzed during the current study are available from the corresponding author on reasonable request.

### Data monitoring {21a}

The data monitoring committee consists of members of the research team and a statistician, who monitor the data independently from the funding agency.

### Adverse events {22}

Evidence on decision coaching trials suggests that adverse events or serious adverse events are not anticipated [28]. Minor adverse events are likewise not anticipated but will be reported to the relevant regulatory bodies as required.

### Auditing trial conduct {23}

The trial steering committee will continually review trial conduct. Formal audits are not planned.

### Protocol amendments {25}

Changes in the study protocol will first be communicated to the funding agency. A revised study protocol will then be sent to the study centers. The clinical trial registry entry will be updated upon changes in the study protocol.

## Dissemination plans {31a}

Results of this trial will be published in scientific journals.

## Discussion

The EDCP-BRCA study is the first study to systematically implement and evaluate structured decision support in healthy *BRCA1/2* mutation carriers worldwide. The purpose of this study is to demonstrate that decision coaching combined with an evidence-based decision aid can improve patient-reported outcomes such as congruence of preferred and actual role in decision-making and satisfaction with the role in the decision-making process. Additional secondary outcomes include improvement in decisional conflict, increased knowledge about prevention options, and lower psychological distress. Another important target of this intervention is to investigate whether structured decision support can be integrated well into current usual care.

Three limitations of the study need to be addressed. First of all, women are informed about the nature of the study and the possibility of receiving decision support. If women are then randomized into the CG and are informed that they do not receive such additional support, there is an increased risk of dropping out of the study. Secondly, since *BRCA1/2* mutations run in families, there is no possibility to prevent family members from entering the study. This could result in some sort of contamination if two siblings are randomized into two different groups. This contamination effect will be analyzed with a family code that is assigned to each family in the German centers for breast and ovarian cancer. Additionally, women in the IG and CG could get in contact online or via self-help groups. Furthermore, due to counseling patients in the IG and the CG, a training effect of physicians might occur and therefore a contamination between IG and CG. Lastly, the intervention is of a complex nature, which includes a decision aid and decision coaching embedded in an optimized standard care setting. Such interventions have the inherent difficulty of attributing an overall effect to one of the components. For this reason, a process evaluation alongside the trial aims to untangle all components of the intervention as well as identify facilitating and inhibitory factors in the implementation.

## Trial status

Study protocol version 1 (06/01/2020)

The recruitment of study participants has started in November 2019 and will continue until January 2021.

## Data Availability

The data set will be available to all principal investigators. The datasets generated for the current study will not be publicly available but will be available from the corresponding author on reasonable request.

## Abbreviations

*BRCA1/2*: Breast cancer susceptibility gene 1/2
CI: Confidence interval
IG: Intervention group
CG: Control group
